## Abstract

**Background:**

In routine intensive care unit (ICU) practice, fluids are often administered without a safety limit, which may lead to fluid overload and decreased survival. Recently, B-lines score (BLS) has been validated as a lung ultrasound (LUS) quantification of pulmonary congestion. This suggests that LUS may provide a safety threshold to conduct fluid therapy and to avoid overhydration. However, there is no randomized study to test the utility of LUS in guiding fluid management in ICU patients by using a pre-specified BLS cut-off value as a threshold for fluid removal.

**Methods:**

LUS Guided Fluid Management Protocol for the Critically Ill Patient is a prospective, multi-centre, randomized controlled trial. Five hundred ICU patients will be randomly assigned in a 1:1 ratio, to protocolized LUS-based fluid management or usual care. The trial intervention will start on ICU admission and will consist in daily assessment of BLS and triggered evacuation of excessive fluids with loop diuretics (Furosemide) when BLS ≥ 15. If rebalancing volume status with diuretics fails, forced evacuation by ultrafiltration will be used. The main endpoint is death from all causes at 28 days from randomization. The secondary outcomes are presence and time-course evolution of organ dysfunctions, ICU- and hospital length of stay, all-cause mortality at 90 days, and health economics data.

**Discussion:**

If study results will show that LUS guided fluid management protocol improves outcome in ICU patients, it will be the base for other studies to refine this protocol or track those categories of critically ill patients to whom it may bring maximum benefits.

**Trial registration:**

ClinicalTrials.gov, NCT03393065. Registered on 8 January 2018.

**Electronic supplementary material:**

The online version of this article (10.1186/s13063-019-3345-0) contains supplementary material, which is available to authorized users.

## Background

In critically ill patients, fluids are used to optimize organ perfusion, compensate fluid losses, avoid fluid deficiency, and deliver medication, antibiotics, or nutrition. However, when in excess, fluids may induce organ dysfunctions [1–3], prolong intensive care unit (ICU) and hospital length of stay [4, 5], and even decrease survival [2–11]. Despite evidence regarding harmful effects of overhydration, in routine ICU practice, fluids are often administered without a safety limit [12] and diuretics are frequently prescribed without an agreement upon what would be the targeted endpoint [13]. These practices may be attributed to the drawbacks of currently used volume assessment methods.

In recent years, LUS has emerge as a novel tool to assess overhydration and has been successfully used in patients from the nephrology [14–19], cardiology [20], and ICU departments [21–24]. LUS has the advantages of being safe, non-invasive, rapidly available, and already part of different diagnostic algorithms for life-threatening conditions [25–27]. Being able to detect in real time the increase of extravascular lung water (EVLW) [28, 29], as well as the response to excessive fluids removal [19, 20], LUS may provide a valuable safety threshold to conduct fluid therapy and to optimize volume status.

The sonographic signs of increased EVLW are the artefacts called B-lines [24, 30–37]. B-lines are hyperechoic, comet-tail artefacts, which emerge from the level of the pleural line and move synchronously with lung sliding [38, 39]. The correlation between B-lines and the amount of EVLW has been demonstrated, by comparing LUS with gold standard methods for EVLW assessment [21, 24, 32]. B-lines presence may be evaluated by scanning the chest, from the second to the fourth intercostal space on the left side, and from the second to the fifth intercostal space on the right side, at parasternal, mid-clavicular, anterior-axillary, and mid-axillary lines, with the patient in supine position [35, 36]. The sum of all B-lines yields a score, B-lines score (BLS), which assess the degree of lung congestion [24, 39]. A BLS < 5 is considered normal, while a BLS > 15 reflects moderate/severe pulmonary congestion [39].

Some prospective studies have shown that a high BLS is linked to a higher risk of mortality in dialysis patients [17, 40] and heart failure patients [41–45]. Few prospective studies have also used LUS as a prognostic tool in critically ill patients [22, 46]. However, there is no randomized study to test the utility of LUS in guiding fluid management in ICU patients, by using a pre-specified BLS cut-off value, as a threshold for fluid removal.

## Study hypothesis

Starting from the premises that mortality may be decreased by avoiding fluid overload and LUS may detect overhydration in early stages, we believe that daily evaluation of BLS, as a refined LUS quantification of pulmonary congestion and triggered evacuation of excessive fluids with diuretics or by ultrafiltration when BLS ≥ 15, may improve outcome in critically ill patients.

Secondary hypotheses are that this intervention is cost-effective and may prevent or, if already present, may improve time-course evolution of organ dysfunctions, may reduce the ICU and hospital length of stay, and increase 90-day survival.

## Objectives

The aim of this study is to evaluate a fluid management protocol for adult ICU patients, based on the daily assessment of BLS using LUS, compared to usual care. A pre-specified BLS cut-off value of 15 will be used in this randomized study to correct fluid overload. The selected cut-off value is recommended by Picano et al. as the limit between absent/mild to moderate/severe lung congestion [39].

## Methods/Design

### Study design

LUS Guided Fluid Management Protocol for the Critically Ill Patient is a multi-centre, randomized controlled two-arm trial, with 1:1 allocation of ICU patients to LUS guided fluid management or usual care.

While hospitalized in the ICU, participants will be randomly assigned to receive LUS guided fluid management or usual care, until ICU discharge or for up to 28 days after randomization, whichever comes first.

The main endpoint will be all-cause mortality at 28 days from randomization (ICU admission).

The Standard Protocol Items: Recommendations for Interventional Trials (SPIRIT) checklist is provided in Additional file 1 and the schedule of study procedures (SPIRIT figure) is shown in Fig. 1.

**Fig. 1 Fig1:**
[figure not shown]
The schedule of study procedures (SPIRIT figure)

### Settings

The trial will be conducted in the ICUs of two university hospitals: Saint Spiridon University Hospital and Regional Institute of Oncology Iasi. The ICUs involved in the trial follow the recommendations of the Society of Critical Care Medicine regarding ICU admission and discharge criteria [47], can deliver the same high level of care, and have physicians capable to provide LUS guided fluid therapy. A rapid response team exists in each of these hospitals and ensures on-demand, hospital ward guidance for the management of patients with deteriorating conditions, as well as the evaluation of patients that may benefit from ICU admission.

### Participants

We aim to enroll 500 adult ICU patients over a period of 24 months. To identify eligible individuals, a daily screening of all critically care admissions will be performed by study investigators. Patients will be included in this study if they are expected to stay at least 48 h in the ICU, meet at least one of the following inclusion criteria, and have none of the exclusion criteria.

#### Inclusion criteria

Major surgeryMajor co-morbidities in surgical patientsPolytrauma with Injury Severity Score (ISS) ≥ 15Acute Physiology and Chronic Health Evaluation II Score (APACHE II) on admission ≥ 10Sequential Organ Failure Assessment Score (SOFA) on admission ≥ 6

#### Exclusion criteria

Patient’s refusalAge < 18 yearsPregnancyPatient with known pulmonary conditions that interfere with the interpretation of LUS: pneumectomy; pulmonary fibrosis; persistent pleural effusionStage 5 chronic kidney disease or indication for emergency renal replacement therapy (RRT)Prolonged resuscitation (≥ 10 min) for cardiorespiratory arrest

### Ethical aspects

The study was approved by the Research Ethics Committee of the Grigore T. Popa University of Medicine and Pharmacy Iasi (date 14 November 2017, number 26261) and by the Research Ethics Committees of each hospital involved in the trial. Patients will receive written information about the nature of the trial, its aims and expected advantages, as well as possible risks, and they will be asked to sign an informed consent. If a patient is unable to give consent at the time of ICU admission, a legally authorized representative may give authorization. Once the participant regains capacity, the individual will be asked to confirm or withdraw consent.

### Randomization and blinding

Study patients will be randomly assigned to either LUS guided fluid management or usual care, in a 1:1 ratio, using block randomization. The randomized block design will be created using a computer-based program by a study team member not involved in patient enrollment and treatment. This team member will securely guard the randomized block design at the coordinating center and will provide the allocation sequence each time a new patient is enrolled. Due to study design, patients and ICU physicians cannot be blinded, but the researcher that investigates primary and secondary outcomes will be blinded to patient group assignment.

### Study interventions

#### LUS guided fluid management (active group)

LUS guided fluid management is based on BLS assessment using LUS, within the first 24 h of ICU admission, and daily thereafter, until ICU discharge, or for up to 28 days after randomization, whichever comes first.

After the initial LUS examination, the follow-up LUS will be performed daily, in the morning, at set times, between 9 am and 11 am. The rationale for this approach is that all ICU patients will have daily, in the morning, a full clinical examination and a complete set of laboratory tests, providing evaluation of fluid status. In this way, all collected data may be further correlated with LUS findings.

LUS examinations will be performed at bedside, with the patient in a supine position, using the 28 zone technique and the GE LOGIQ V2® ultrasound system with the GE 3Sc-RS Cardiac Sector Probe® (1.5–4.0 MHz frequency). The focus of the image will be set at the level of the pleural line and the depth of penetration at around 4–8 cm. The image will be optimized by regulating the gain. The lungs will be scanned, from the second to the fourth intercostal space on the left side, and from the second to the fifth intercostal space on the right side, at parasternal, mid-clavicular, anterior-axillary, and mid-axillary lines. B-lines will be recorded in each intercostal space (28 sites of examination). The sum of all B-lines will produce a score, BLS, reflecting the extent of EVLW accumulation.

The ICU physician may recommend fluid therapy or vasoactive drugs with types and amounts at his/her choice. However, when signs of moderate/severe pulmonary congestion are seen on LUS exam (BLS ≥ 15), a negative 24-h fluid balance (250–1000 mL) will be intended according to clinical judgement.

To achieve this goal, a protocolized intravenous administration of furosemide will be used, under careful monitoring of diuretic response. Diuretic administration will start with a furosemide dose ≤ 80 mg/day which will be further adapted based on the next 24-h fluid balance, the follow-up BLS, and the previous diuretic regimen. If a negative fluid balance of > 1000 mL/24 h is obtained and BLS is still ≥ 15, the initial dose of diuretic will be reduced. If a negative fluid balance of < 1000 mL/24 h is obtained and BLS is still ≥ 15, the administered diuretic dose will be maintained. If negative fluid balance is not achieved and BLS is still ≥ 15, the dose of diuretic will progressively be increased until the goal is attained. The maximum dose of furosemide will not exceed 800 mg/day.

In case of a fall in blood pressure or an increase in creatinine blood level that is perceived to be due to a transient episode of intravascular fluid depletion, the diuretic may be temporarily stopped or the dose may be decreased according to clinical judgement. After the patient has stabilized and if BLS is ≥ 15, diuretics will be reinitiated until the patient’s BLS is < 15. If the target of depleting overhydrated patients with diuretics cannot be achieved, RRT will be used. For RRT, the treating physician may choose between slow continuous ultrafiltration, continuous veno-venous hemofiltration, continuous veno-venous hemodialysis, or continuous veno-venous hemodiafiltration. Along with the goal of rebalancing fluid status, the choice of RRT technique should rely on patients’ particularities and other goals of homeostasis restoration.

As acute kidney injury (AKI) is often present in ICU patients, and RRT is a common procedure during critical care, to avoid bias, AKI will be diagnosed in all patients based on changes in the serum creatinine, urine output, or both, according to the KDIGO recommendations [48].

In AKI patients, the following criteria for RRT initiation will be used:Stage 3 AKI (urine output < 0.3 mL/kg/h for ≥ 24 h and/or > 3-fold increase in serum creatinine level compared with baseline, or serum creatinine of ≥ 4 mg/dL with an acute increase of at least 0.5 mg/dL within 48 h)Urine production < 200 mL/12 h or anuriaSerum potassium level > 6 mEq/L and/or with electrocardiographic abnormalitiesOrgan edema in the presence of AKI resistant to diuretic treatmentA pH < 7.15 in the context of either pure metabolic acidosis or mixed acidosisAcute pulmonary edema due to fluid overload responsible for severe hypoxemia despite diuretic therapy

The algorithm of study protocol is shown in Fig. 2 and the recommended diuretic regimen in patients with BLS ≥ 15 is shown in Table 1.

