**Fig. 2 Fig2:**
[figure not shown]
Algorithm of study protocol

**Table 1 Tab1:** Recommended intravenous diuretic regimen in patients with BLS ≥ 15

	Furosemide (mg/day)	
	Previous daily dose	Recommended daily dose
1	≤ 80	40 mg i.v. bolus + 5 mg/h
2	81–160	80 mg i.v. bolus + 10 mg/h
3	161–240	80 mg i.v. bolus + 20 mg/h
4	> 240	80 mg i.v. bolus + 30 mg/h

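### The furosemide rules in the text and Table 1 are not reconciled: the article does not say whether the table sets the first dose or only the step up, and it omits the text's fluid-balance rules.

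*Protocol article*

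**What the plan says.** Under LUS guided fluid management (active group), the protocol article gives a start and three adjustment rules, all for patients whose BLS is 15 or more:

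- Start: "Diuretic administration will start with a furosemide dose ≤ 80 mg/day". Later doses depend on the fluid balance over the following 24 h, the repeat BLS and the regimen already given.
- Negative balance above 1000 mL in 24 h: "the initial dose of diuretic will be reduced".
- Smaller negative balance: "If a negative fluid balance of < 1000 mL/24 h is obtained and BLS is still ≥ 15, the administered diuretic dose will be maintained".
- No negative balance: "If negative fluid balance is not achieved and BLS is still ≥ 15, the dose of diuretic will progressively be increased until the goal is" reached, with a ceiling of 800 mg/day.

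The same section then refers to Table 1 as "the recommended diuretic regimen in patients with BLS" of at least 15, and the table's caption says the same. The table has two columns, previous daily dose and recommended daily dose. Its first row covers a previous dose of 80 mg/day or less and recommends "40 mg i.v. bolus + 5 mg/h". The remaining rows are an 80 mg bolus plus 10, 20 or 30 mg/h, for previous doses of 81–160, 161–240 and above 240 mg/day.

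**The concern.** The text and the table address the same patients on the same trigger but use different inputs. The text fixes a low start and lets fluid balance set the direction of change. The table asks only what the patient had before, and a patient who has had no furosemide falls in its first row. Nothing printed says which governs the first dose, or that the table is used only when the text calls for an increase.

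This regimen is the protocolized part of the experimental treatment, given to critically ill patients at two hospitals. If the sites resolve the ambiguity differently, the dose delivered in the active arm will differ by site for reasons unrelated to the patient. The section on strengths and limitations also plans to record and analyse departures from the diuretic regimen. That analysis needs one reference rule.

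**Working it through.** **Inputs.** Boluses, hourly rates and previous-dose bands come from Table 1. The 80 mg/day starting limit, the balance rules and the 800 mg/day maximum come from the active-group text. The infusion duration is not stated and is an assumption here, so a range is shown.

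**Formula.** Daily total = bolus + hourly rate × infusion hours.

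**The plan's own figure first.** Row 4 over 24 h gives 80 + 30 × 24 = 800 mg, exactly the stated maximum. This supports a 24-h infusion with the bolus counted, as does the column being a daily dose.

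**All rows (mg/day):**

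| Infusion hours | Row 1 (≤ 80) | Row 2 (81–160) | Row 3 (161–240) | Row 4 (> 240) |
|---|---|---|---|---|
| 24 | 40 + 5×24 = 160 | 80 + 10×24 = 320 | 80 + 20×24 = 560 | 80 + 30×24 = 800 |
| 12 | 100 | 200 | 320 | 440 |
| 8 | 80 | 160 | 240 | 320 |
| 6 | 70 | 140 | 200 | 260 |

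**Start dose.** At 24 h, row 1 is 160 / 80 = 2 times the text's upper limit, so at least twice any start the text permits. The infusion alone is 5 × 24 = 120 mg, also above 80. Row 1 stays within 80 mg only if the infusion lasts (80 − 40) / 5 = 8 h or less. At 8 h, rows 1 to 3 equal the upper ends of their own bands, so arithmetic alone does not exclude that reading. But row 4 would then total 320 mg, and the table would never approach the 800 mg maximum.

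**Direction of change.** At 24 h, each of rows 1 to 3 exceeds the top of its band (160 > 80, 320 > 160, 560 > 240), and row 4 gives the maximum. The table therefore never lowers a dose, and holds one only at 800 mg. Take a patient on 160 mg/day with a negative balance above 1000 mL and BLS still 15 or more. The text reduces the dose; row 2, read as captioned, gives 320 mg. At 8 h row 2 gives 160 mg, which is still not a reduction.

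**What does not depend on duration.** At any infusion time the table has no fluid-balance input, so by itself it cannot express the text's three-way rule.

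**The case against.** The strongest reply is that text and table are complementary. The text's start of 80 mg/day or less matches the first previous-dose band, which fits a table that takes over after the start. The text also lists the previous regimen among its inputs. On this reading fluid balance sets the direction, and the table sets the step size when the direction is up. A site that doubled the dose after a strong response would be overriding an explicit instruction to reduce. Fig. 2, the study algorithm, may show this link, and it is not shown in the copy reviewed.

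Much of this stands. The complementary reading is plausible and would remove both conflicts. What remains is that neither the sentence introducing the table nor its caption limits it to escalation. The latitude left to clinicians covers the balance target and episodes of low blood pressure or rising creatinine, not the choice between text and table.

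A reader might go further and infer that the tested intervention is undefined, that deviations cannot be classified, or that sites must differ two-fold on the first day. The documents do not support that. The two-fold figure needs both a 24-h infusion and Table 1 governing the first dose. Opposite directions arise only if the table is applied without the text's balance rules.

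Two further details are secondary. Followed day by day at 24 h, the table runs 160, 320, 800 and skips the 161–240 row, but that band can still be entered from other doses. The shift from initial to administered dose between two rules is loose wording.

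**Conclusion.** The inconsistency is real and is printed in the article; it is not a detail lost in condensation. Its size is conditional. With a 24-h infusion and Table 1 read as captioned, the table's lowest regimen is 160 mg/day against a starting limit of 80 mg/day, and the table escalates where the text reduces or maintains. With an infusion of 8 h or less, or with the table confined to escalation, the start-dose conflict disappears. Confining the table to escalation would also settle the titration conflict, but the article does not say that this is meant. The planned intention-to-treat comparison is not invalidated. What suffers is consistency of the delivered treatment and the reference for judging adherence. No view is taken on which dose or rule is right.

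**What to change.** Reconcile the active-group text, Table 1 and Fig. 2 into one rule. It should state:

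- whether Table 1 is the starting regimen or applies only when the text calls for an increase;
- what the previous-dose column refers to (treatment before the trigger, or the last dose given under the protocol);
- how long the infusion runs each day;
- whether the bolus counts toward the daily total.

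The clinical leads decide which figures stand. Send the clarification to both sites and classify deviations from the diuretic regimen against the reconciled rule.

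The cost is a protocol clarification or amendment and a site memo. There is one small downside. The Trial status section puts enrolment from November 2017 to October 2019, so a clarification during that period may change delivered dosing between earlier and later patients. Its date should be recorded so that the adherence analysis can take account of it.

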**Fig. 2 Fig2:**
[figure not shown]
Algorithm of study protocol

**Table 1 Tab1:** Recommended intravenous diuretic regimen in patients with BLS ≥ 15

	Furosemide (mg/day)	
	Previous daily dose	Recommended daily dose
1	≤ 80	40 mg i.v. bolus + 5 mg/h
2	81–160	80 mg i.v. bolus + 10 mg/h
3	161–240	80 mg i.v. bolus + 20 mg/h
4	> 240	80 mg i.v. bolus + 30 mg/h

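### Table 1's furosemide regimens do not fit the table's own dose bands or the titration rules in the text, so the same patient-day can support either 560 or 800 mg/day

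*Protocol article*

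**What the plan says.** The titration rules are in the protocol article, Study interventions, LUS guided fluid management (active group). Treatment begins at no more than 80 mg/day of furosemide. It is then adjusted on three things: the following 24-h fluid balance, the repeat B-lines score (BLS) and the diuretic regimen already given. While BLS stays at 15 or above:

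- with a negative balance of more than 1000 mL in 24 h, the dose is lowered;
- with a negative balance of less than 1000 mL, the dose is kept;
- with no negative balance, "the dose of diuretic will progressively be increased until the goal is attained".

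The ceiling is explicit: "The maximum dose of furosemide will not exceed 800 mg/day". If diuretics fail, renal replacement therapy follows.

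Table 1 is titled "Recommended intravenous diuretic regimen in patients with BLS ≥ 15", works in mg/day, and has one column for the previous dose and one for the recommended dose:

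- Row 1 takes patients whose previous dose was at most 80 mg/day and recommends "40 mg i.v. bolus + 5 mg/h".
- Row 2 takes previous doses from 81 up to 160 mg/day; both the bolus and the hourly rate are twice those of row 1, at 80 mg and 10 mg/h.
- Row 3 takes previous doses from 161 up to 240 mg/day and recommends "80 mg i.v. bolus + 20 mg/h".
- Row 4 takes any previous dose above 240 mg/day; the bolus stays at 80 mg and the hourly rate rises to 30 mg/h.

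The table has no column for fluid balance. Neither it nor the text says how many hours the infusion runs, whether the bolus is repeated each day, or whether the bolus counts towards the next day's previous dose.

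**The concern.** The bands on the left of Table 1 and the regimens on the right are in the same daily unit, and BLS is re-measured every day. A site can naturally take today's regimen as tomorrow's previous dose. The two sides should then connect, and on the most direct reading they do not.

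This table defines the active-arm treatment. If it supports two prescriptions for one patient-day, the two sites can give different exposures while both believe that they comply, and some patients can reach the protocol maximum a step sooner than others with the same response. It also weakens a safeguard that the article offers under Strengths and limitations, where departures from the diuretic regimen are to be documented and examined. Adherence cannot be classified against a regimen with two readings.

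**Working it through.** **Inputs.** Boluses, hourly rates and bands come from Table 1. The 800 mg/day ceiling and the keep, lower and increase rules come from the active-group text. The infusion duration is not given; 24 h is an assumption.

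**Step 1: reproduce the ceiling.** Daily total = bolus + 24 × hourly rate. Row 4: 80 + 24 × 30 = 800 mg. This equals the stated maximum exactly, which supports the assumption without proving it.

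**Step 2: all rows, and the row each total leads to.**

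| Row | Bolus + 24 h infusion | Next row | Infusion only | Next row |
|---|---|---|---|---|
| 1 | 40 + 120 = 160 mg | 2 | 120 mg | 2 |
| 2 | 80 + 240 = 320 mg | 4 | 240 mg | 3 |
| 3 | 80 + 480 = 560 mg | 4 | 480 mg | 4 |
| 4 | 80 + 720 = 800 mg | 4 | 720 mg | 4 |

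With the bolus counted, no total falls in 161–240 mg. From any previous dose of 80 mg/day or less, the sequence is 160, 320, 800 mg/day (rows 1, 2, 4). The last step is 800 − 320 = 480 mg, or 800 / 320 = 2.5-fold. With infusion only counted, the sequence visits rows 1, 2, 3 and 4.

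**Step 3: the ambiguous day.** After a full day of row 2, the previous dose is 320 mg (bolus counted) or 240 mg (not counted). The first leads to row 4, 800 mg in total; the second leads to row 3, 560 mg in total.

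**Step 4: partial days.** Row 2 run for h hours delivers 80 + 10h mg. This lies in 161–240 for h from (161 − 80)/10 = 8.1 to (240 − 80)/10 = 16 hours. If the amount delivered is what counts, an interrupted row 2 leads to row 3 and an uninterrupted one to row 4. The text allows temporary stops for falls in blood pressure or rises in creatinine, so partial days are foreseeable.

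**Step 5: the table against the keep and lower rules.** In rows 1 to 3 the full-day total exceeds the top of the row's own band: 160 against 80, 320 against 160, 560 against 240. Row 4 gives 800 mg for anything above 240. Applied daily to every patient with BLS of 15 or more, the table never lowers a dose within the ceiling, and keeps one only at 800 mg. For example, a patient who received 160 mg, has a negative balance under 1000 mL and still has BLS of 15 or more is kept at that dose by the text but moved to row 2 (320 mg) by the table.

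**The case against.** The strongest reply is that Table 1 is not described as an escalation ladder. It is a recommended regimen indexed by prior dose, and the daily decisions belong to the text. Read as an entry table, row 3 serves patients already on 161–240 mg/day. The lack of a fluid-balance column even suggests that the table was not meant to be the daily rule by itself. The algorithm figure (Fig. 2), which might settle how the two fit together, is not available here. Bypassing row 3 also depends on a 24-h infusion with the bolus counted, and the infusion-only reading removes it.

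Much of this stands. It rules out saying that row 3 can never be reached, or that the table is simply an arithmetic error. It does not remove the point. No available text limits the table to entry, and the text names the earlier regimen as a basis for later adjustment. That two reasonable conventions give different next doses is itself the fault.

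A reader might also infer that 160, 320, 800 contradicts the progressive increase in the text. It does not: the sequence rises at each step, stays within the ceiling, and the text fixes no step size. Nor do the documents show that a row 3 step was intended for every patient, or support any figure for an effect on 28-day mortality. Monitoring, discretion to stop or reduce, and daily collection of diuretic data all remain in place.

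**Conclusion.** The point holds as an internal inconsistency and an under-specified regimen. On bolus plus 24 h of infusion, which is an assumption supported by row 4 matching the ceiling, Table 1 yields 160, 320, 560 and 800 mg/day. Repeated full-day use from 80 mg/day or less then bypasses row 3, which is reached only from an existing dose of 161–240 mg/day or after a partial-day infusion. On infusion only, all four rows are visited. The practical size is a difference of 800 − 560 = 240 mg/day for the same patient after the same full day of row 2, decided by a convention that the protocol does not state.

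Separately, daily use of the table for all patients with BLS of 15 or more conflicts with the text's keep and lower rules under either convention. This part does not depend on how the bolus is counted, only on whether the table is applied at each reassessment. The matter bears on safety and on the definition of the intervention. The documents do not show which reading was meant, and this review takes no position on it.

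**What to change.** Reconcile Table 1 with the titration rules in the active-group text:

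- show each row's 24-h total in the table;
- state the infusion duration, and whether the bolus counts in the previous daily dose;
- state whether the table applies only at entry or at each daily reassessment and, if daily, how it combines with the fluid-balance rules;
- make bands and totals consistent with that use, and check that Fig. 2 agrees.

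All dose values and dosing rules, including how an interrupted infusion is counted, are for the trial's clinical leads to decide.

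The cost is a corrected table and a sentence or two in a protocol amendment, passed on to the two sites. It needs no extra patients or procedures.
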